## Design

LABOR is a randomized, controlled, non-inferiority trial. Patients will be randomly allocated to receive a mesh repair of their incisional hernia with either laparoscopic bridging or open anatomical reconstruction. The trial has been registered on Current Controlled Trials as ISRCTN93729016.

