### Sample size calculation, randomization and statistical analysis

On the basis of a previous published work, the minimum DLL to define the non-inferiority of laparoscopic bridging vs. anatomic open reconstruction will be set to 5 degrees with a standard deviation of 8.5 degrees. With this hypothesis and for a power of 90% and an alpha of 5%, we will need 50 patients in each arm (total 100). If we consider a possible dropout rate of 10%, a total of 110 patients would be sufficient. As a consequence, approximately 20 patients for each center will be required.

A centralized block randomization stratified for center will be performed by a statistician not involved in patient management. Blocks will have a variable dimension (random) between 4 and 12 units. A total of five blocks will be obtained for each center in the event that the investigator continues enrollment beyond the initially planned sample size. The local investigators, after obtaining written informed consent of patients, will receive the randomization arm from the statistical center for each patient, then the patient will be allocated to the treatment group as indicated.

Data analysis will be performed by a statistician not involved in data collection at the main investigation center (University of Genoa). The means and standard deviations or medians with ranges, if asymmetry of data is detected, will be reported for all continuous demographic and clinical characteristics recorded, whereas counts and percentages will be recorded for categorical characteristics (e.g., gender, functional status and smoking habits).

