To compare the DLL test results during follow-up between the two groups of treatment, ANOVA for repeated measures will be adopted using DLL as the dependent variable. Because the DLL test cannot have a normal distribution, a ranking transformation will eventually be used. The same approach will be used for the other ordinal characteristics used as secondary outcomes (VAS as scoring for pain and AWS score) and, in general, for all other outcomes considered. If a consistent number of missing values is detected during the follow-up, ANOVA for repeated measures will be replaced by linear mixed or generalized estimating equation (GEE) models, which permit the exclusion of the data only from a single missing observation and not from the patient on overall as with ANOVA. Single comparisons between baseline values and each time during follow-up will be assessed using Bonferroni correction for multiple comparisons. All analyses will be performed on an intention-to-treat basis. A *p*-value lower than 0.05 will be considered statistically significant. SPSS (v.20, IBM Corp., Armonk, NY, USA) will be used for the statistical analyses.

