### Outcomes

#### Primary outcome

Changes in baseline DLL measures at 12 months postoperatively in both groups.

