#### Secondary outcome

Among the subjects in each group of treatment, the secondary outcomes are as follows:

•differences in DLL (preoperation and at 1 and 6 months postoperation)

•differences in TR test (preoperation and at 1, 6 and 12 months postoperation)

•AWS score (preoperation and at 1, 6 and 12 months postoperation)

•respiratory function tests (preoperation and at 6 and 12 months postoperation)

•intraabdominal pressure (preoperation and postoperation)

•pain

•quality of life (SF36, preoperation, postoperation, 1 month postoperation, 6 months postoperation and 12 months postoperation)

•recurrence rate in each group

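### The trial is sized for a between-arm difference at 12 months, but the only visit-specific tests the plan fixes are comparisons with baseline

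*Protocol article*

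**What the plan says.** All references are to the Protocol article.

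- *Design*: "LABOR is a randomized, controlled, non-inferiority trial".
- *Aim of the study*: the target is the difference between the groups in DLL one year after surgery.
- *Sample size calculation, randomization and statistical analysis*: "the minimum DLL to define the non-inferiority of laparoscopic bridging vs. anatomic open reconstruction will be set to 5 degrees". The SD is taken as 8.5. The size that results is given thus: "for a power of 90% and an alpha of 5%, we will need 50 patients in each arm".
- Same section, analysis paragraph: DLL during follow-up is compared between the two groups by repeated-measures ANOVA, with mixed or GEE models if many values are missing. The significance threshold is p below 0.05. The paragraph then adds: "Single comparisons between baseline values and each time during follow-up will be assessed using Bonferroni correction for multiple comparisons". It does not say whether these comparisons are made within each arm or pooled over arms, how many there are, or whether they decide the primary outcome.
- The statement under *Primary outcome* reads: "Changes in baseline DLL measures at 12 months postoperatively in both groups".
- The list under *Secondary outcome* opens with this line: "Among the subjects in each group of treatment, the secondary outcomes are as follows".
- *Performance and measures: double leg-lowering test*: measured before surgery and at 1, 6 and 12 months.

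**The concern.** The sized question is one contrast: bridging minus reconstruction, at 12 months, against 5 degrees. No analysis named in the plan delivers it.

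The ANOVA compares the groups over all of follow-up. A group effect averages over visits, and a group-by-time interaction picks up any divergence at any visit. Neither is the 12-month difference, and neither refers to the margin.

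The tests that do look at a single visit compare that visit with baseline. Whether run per arm or pooled, they set aside the randomised comparison and mix the effect of the repair with healing, practice with the test and regression to the mean. One arm changing significantly while the other does not is no evidence that the arms differ. Both arms changing significantly is no evidence that they are alike.

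The outcome sections add to the mismatch, because their wording (changes in both groups, outcomes in each group) matches the before/after tests better than it matches the stated aim.

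**Working it through.** **1. The plan's own figure.** Inputs from the sample-size section: margin 5, SD 8.5, power 90%, alpha 5%. For a between-arm non-inferiority comparison of means with a true difference of 0:

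n per arm = 2 × [8.5 × (z_alpha + z_power) / 5]²

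- One-sided 5%: 2 × [8.5 × (1.645 + 1.282) / 5]² = 49.5, rounded up to 50. This is the stated number.
- One-sided 2.5% (equivalently two-sided 5%): 2 × [8.5 × (1.960 + 1.282) / 5]² = 60.7, rounded up to 61.

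So the 50 per arm belongs to a between-arm contrast tested once, at one-sided 5%. The standard error of that contrast is 8.5 × √(2/50) = 1.70. If the repairs are equal, non-inferiority is shown with probability Φ(5/1.70 − 1.645) = 90%.

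**2. What the named analyses estimate.**

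| Analysis in the plan | Contrast | Uses randomisation | At 12 months | Against 5 degrees |
|---|---|---|---|---|
| Repeated-measures ANOVA (or mixed/GEE) | groups, over follow-up | yes | not isolated | no |
| Bonferroni single comparisons | each visit versus baseline | no | yes, as one of the visits | no |
| Sized question | bridging versus reconstruction | yes | yes | yes |

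No analysis row matches the last row.

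**3. What an arm-by-arm reading would do.** This is a what-if, since the plan does not state such a rule. With three postoperative DLL visits, the level per comparison within an arm would be 0.05/3 = 1.67%. That level is derived here; the plan does not give it, and counting both arms would make it 0.05/6 = 0.83%. Assume 50 evaluable per arm, independent arms, two-sided paired t-tests and an SD of change of 8.5. The document gives 8.5 without saying whether it refers to the value or the change. If p is the power in one arm, two equal repairs get opposite verdicts with probability 2p(1 − p).

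| True change in both arms (degrees) | p | 2p(1 − p) |
|---|---|---|
| 0 | 0.017 | 3% |
| 1 | 0.057 | 11% |
| 2 | 0.218 | 34% |
| 3 | 0.511 | 50% |
| 4 | 0.798 | 32% |
| 5 | 0.950 | 10% |
| 6 | 0.993 | 1% |

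Discordance reaches 20% only for true changes of about 1.5 to 4.4 degrees. With an SD of change of 6 the range is about 1.1 to 3.1, and with 12 it is about 2.1 to 6.3.

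**4. The opposite error.** Let the arms truly improve by 4 and 9 degrees, a deficit equal to the margin. Assume a baseline/12-month correlation of 0.6, so the SD of change is 8.5 × √(2 × 0.4) = 7.60 and the standard error within an arm is 7.60/√50 = 1.075. In the normal approximation, power is Φ(4/1.075 − 2.394) = 0.91 in the weaker arm and practically 1 in the other. Both are significant about 91% of the time (82% to 97% for correlations of 0.5 to 0.7).

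**The case against.** The analysis paragraph opens with a randomised between-group ANOVA at p below 0.05. The Bonferroni sentence comes afterwards, covers only comparisons with baseline, and is a routine supplement to such a model. The abstract, the aim, the margin and the section on clinical implications all pose the question between arms. No passage concludes anything from one arm being significant and the other not. Visit-specific contrasts are often left to an analysis plan, and none is shown here.

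Most of this stands, and it rules out three stronger readings that a reader might infer:

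- *The 12-month result is judged arm by arm at 1.67% instead of between arms at 5%.* The planned between-group ANOVA contradicts this, and neither the arm-by-arm rule nor the 1.67% is in the text.
- *Equal repairs will often get opposite verdicts.* This depends on the true change and its SD. The document gives no expected change and does not identify 8.5 as the SD of change. Discordance is small near 0 degrees and small again above about 5.
- *Bonferroni costs the primary comparison power.* The text attaches the correction only to comparisons with baseline, so the between-arm test keeps its level.

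That the article reads a non-significant difference as acceptance of the null hypothesis is a separate matter and is not counted here.

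One part of the objection does not stand. The plan does not leave the visit-specific tests open: it fixes them, on a contrast that cannot answer the sized question. Followed exactly, it yields no 12-month between-arm estimate to set against 5 degrees.

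**Conclusion.** The point holds in a limited form. The between-arm ANOVA exists, but it covers the whole of follow-up, and the only tests tied to a visit are comparisons with baseline. The contrast for which 50 per arm was calculated therefore has no matching named analysis, and the outcome wording makes a before/after reading possible. This conclusion rests on the text alone.

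The figures on misleading verdicts (3% at no change, up to 50% near 3 degrees, about 1% at 6 degrees; both arms significant about 91% of the time despite a deficit equal to the margin) show only what would happen if the result were read arm by arm. They rest on assumed SDs of change of 8.5 and 7.6 respectively, 50 evaluable patients per arm, a level of 0.05/3 and chosen true changes. They are not a prediction for the trial. The plan should be changed, because the mismatch touches the primary question and is simple to remove.

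**What to change.** - Name as the primary analysis the between-arm difference in DLL change from baseline at 12 months, or the baseline-adjusted difference, estimated from the repeated-measures or mixed model already planned.
- Report it in degrees with a confidence interval, and compare that interval with the 5-degree margin at the planned alpha, without Bonferroni correction. State the sidedness, since 50 per arm reproduces only at one-sided 5%.
- Label the baseline-versus-visit comparisons as descriptive.
- Reword *Primary outcome* and *Secondary outcome* as differences between groups, in line with the aim.

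The cost is one analysis sentence and two outcome statements. The visits and measurements stay as they are, and no new data are needed. The number of patients also stays the same if the planned alpha is one-sided 5%.

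### All analyses of a declared non-inferiority trial are fixed as intention-to-treat, so nothing checks whether departures from the assigned repair have diluted the difference between bridging and reconstruction

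*Protocol article*

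**What the plan says.** The Design section of the protocol article states: "LABOR is a randomized, controlled, non-inferiority trial". Under Sample size calculation, randomization and statistical analysis, the DLL margin "will be set to 5 degrees with a standard deviation of 8.5 degrees". With 90% power and an alpha of 5%, this leads to 50 patients per arm. The primary outcome is "Changes in baseline DLL measures at 12 months postoperatively in both groups".

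The analysis population is set in one sentence of the same statistical section: "All analyses will be performed on an intention-to-treat basis". The article names no per-protocol, as-treated or other supportive set. It does not say how a laparoscopic case converted to open surgery, or an open case whose midline cannot be closed, would be classified. The only intraoperative departure it mentions is unplanned resection (section Postoperative), which is left to the operating surgeon.

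The decision rule given is "A *p*-value lower than 0.05 will be considered statistically significant". The analysis text does not mention a comparison with the 5-degree margin.

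**The concern.** When a patient receives the other arm's repair but is analysed as randomised, the two arm means tend to move together. In a superiority trial this works against the claim. In a non-inferiority trial it works for it, which is why ITT is usually accompanied there by an analysis of patients treated as assigned.

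The protocol's wording makes this relevant. Aim of the study asks about the role of reconstruction compared with simple bridging. Clinical implications would conclude from similar results that bringing the rectus muscles to the midline brings the patient no benefit, and explains this by scarred tissue or by defects too small to matter. Those are statements about the repair performed. If some Group R patients did not have the midline closed, or some Group B patients did, similar ITT means could partly reflect that mixing, and the plan has no analysis that would show it.

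**Working it through.** **Inputs from the article (statistical section).** Margin 5 degrees, SD 8.5 degrees, power 90%, alpha 5% (sidedness not stated), 50 per arm.

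**Input assumed.** Net crossover c, meaning the fraction of Group B who in effect received reconstruction plus the fraction of Group R who in effect were bridged. The article gives no rate, so a range of 0 to 20% is shown. Because c is a sum, 10% could be 5% in each arm; 10% in each arm would be c = 20%.

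**Step 1: reproduce the stated sample size.** For a true difference of zero, n per arm = 2 × SD² × (z₁₋α + z₁₋β)² / margin².
- One-sided 5%: 2 × 72.25 × (1.645 + 1.282)² / 25 = 49.5, rounded up to **50**. This matches the article.
- One-sided 2.5%: 2 × 72.25 × (1.960 + 1.282)² / 25 = 60.7, rounded up to 61. This does not match.

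The stated size is therefore that of a one-sided 5% test against the margin, and that test is used below.

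**Step 2: standard error.** SE = 8.5 × √(2/50) = 1.70 degrees.

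**Step 3: dilution.** Let the true deficit of bridging equal the margin, and let each deviating patient carry the full effect of the other repair. The expected ITT difference is 5 × (1 − c). The chance of declaring non-inferiority is Φ(5c / 1.70 − z₁₋α).

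| Net crossover c | Expected ITT deficit (degrees) | False non-inferiority, one-sided 5% | One-sided 2.5% |
|---|---|---|---|
| 0% | 5.00 | 5.0% | 2.5% |
| 2% | 4.90 | 5.6% | 2.9% |
| 5% | 4.75 | 6.7% | 3.5% |
| 10% | 4.50 | 8.8% | 4.8% |
| 20% | 4.00 | 14.5% | 8.5% |

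For example, at c = 10% and one-sided 5%: Φ(0.5/1.70 − 1.645) = Φ(−1.351) = 0.088. Here, false means false about the repairs as performed.

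**Step 4: power of a per-protocol set.** Power = Φ(5 / (8.5 × √(2/m)) − 1.645), with m patients per arm and a true difference of zero.
- 5% excluded, m = 47.5: SE 1.744, power 88.9%.
- 10% excluded, m = 45: SE 1.792, power 87.4%.

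**The case against.** **The question being asked.** For the choice of which approach to offer, ITT keeps its nominal error rate whatever the conversions. The abstract's Discussion, which speaks of choosing an intervention for a patient, supports that reading. This stands, and it limits the concern to the effect of the repair received. It does not remove it, because Aim of the study and Clinical implications also draw conclusions about the repair itself.

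**Direction.** A reader might infer that poor adherence must favour bridging. The documents do not support that. A converted case may be a harder one that recovers worse, and it may not receive the Rives-Stoppa repair planned for Group R. Keeping such a patient in Group B could widen the difference against bridging. Full dilution is an assumption.

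**Rate.** The design points to few deviations. Defects are limited to 10 cm and chosen as suitable for both techniques, previous mesh repair and acute presentations are excluded, and surgeons have done at least 20 cases of each procedure. At 2% net crossover the error rises by 0.6 percentage points, and at 0% not at all. The documents offer no support for the 20% row. They do not exclude deviations either: the Background describes re-approximation of the muscles as limited by what is achievable.

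**The test.** The error rates presuppose a test against the margin, whereas the analysis text plans a repeated-measures ANOVA, possibly on ranks, with p < 0.05. This stands as a limit on the figures. The absent margin comparison is a separate and more basic problem.

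**The SAP.** Supportive populations are often left to an SAP, and none is shown. But the article does more than stay silent here: its sentence covers every analysis. It could be read as naming only the primary principle, in which case the fix is a clarification.

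**Conclusion.** The concern holds as a moderate one. The plan commits a non-inferiority trial to ITT throughout and leaves its conclusion about midline reconstruction without a check on dilution. The false non-inferiority rate for the repair-received question ranges from the nominal 5.0% with no crossover, through 5.6% at 2% and 8.8% at 10%, to 14.5% at 20%. These figures rest on full dilution, a true deficit exactly at the margin, 50 evaluable patients per arm, SD 8.5 degrees, a one-sided 5% margin test and a crossover rate that the article does not give.

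A reader might infer that ITT is the wrong primary analysis or that a non-inferiority result would be invalid. Neither follows: ITT answers the policy question correctly, and the inflation is a possibility of unknown size, not an established error.

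**What to change.** Keep ITT as the primary analysis. Amend the analysis-population sentence in the statistical section, before analysis, to add:

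1. **A CRF item** recording the repair actually performed: approach, conversion, and whether the midline was closed or bridged.
2. **A pre-specified supportive per-protocol analysis** of the same 12-month DLL contrast, in patients who received the assigned repair (midline closed in Group R, laparoscopic bridging in Group B), with the classification of conversions defined in advance.
3. **A reporting rule:** give the confidence interval from each analysis against the 5-degree margin, side by side, and discuss any discordance before claiming non-inferiority. This presupposes that the comparison with the margin is itself written into the plan.
4. **A statement of which question each analysis answers:** approach offered (ITT) or repair received (per-protocol).

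The cost is one CRF item and one further analysis. The 12-month CT already planned to assess interrectal distance gives supporting evidence on midline status. The downside is that the per-protocol set is smaller, with the power shown above, and is selected after randomisation, so it may lose the harder cases. It supports ITT and does not replace it. In that supportive role it does not require a larger trial. If the per-protocol set itself had to hold 100 evaluable patients after 10% dropout, 5 to 10% exclusions would need 100/(0.90 × 0.95) = 117 to 100/(0.90 × 0.90) = 124 randomised, against the 110 planned.

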### Participants

The researchers will recruit consecutive patients who are affected by an incisional hernia scheduled for surgical repair and meet the criteria for enrollment over a period of approximately 1 year. The patients in the participating units will be screened daily. Demographic data on screened patients, regardless of meeting enrollment criteria, will be recorded (registry: age, gender and type of surgery). We will randomize 110 patients admitted into the participating centers. It is expected that each participating center will randomize at least 20 patients who will meet all of the inclusion criteria.

Based on the current literature [19], it was decided to enroll patients with a defect suitable for both laparoscopic and open repair. For this reason, we have set the upper limit of the defect size at a width of 10 cm. We decided to set 60 years old as the cutoff age because that is the mean age in recent high-quality, randomized studies [4], and this cutoff value will minimize the difference in trunk flexor strength observed in previously cited papers and generated by differences in age [17].

### Inclusion criteria

Patients will be eligible for study enrollment if they meet the following criteria:

(1) Presence of a midline incisional or a ventral primitive hernia [15]

(2) Dimension of the defect measured on preoperative CT scan is as follows:

(a) Primary ventral hernia ≥4 to ≤10 cm at its greatest diameter according to a preoperative CT scan (“large” according to EHS classification for primary ventral hernia) [20]

(a) Incisional hernia ≥4 to ≤10 cm at its greatest diameter according to a preoperative CT scan (W2 according to EHS classification for incisional hernias [20])

3 Both genders

4 ≥60 years of age

5 Provide informed consent for randomization

### Exclusion criteria

1. Patients with non-midline defects or diastasis recti without herniation

2. BMI ≥ 35 kg/m^2^

3. Hernia with a previous mesh repair attempt

4. Patients classified as American Society of Anesthesiologists class 4 or 5

5. Patients with a severe comorbid condition likely to limit survival to 2 years

6. Patients with cirrhosis with or without ascites

7. Patients under immunosuppressive treatment

8. Patients with acute bowel obstruction, strangulation, peritonitis or perforation

9. Presence of local or systemic infection

10. Patients with neuromuscular disease likely to impair motility (e.g., previous ictus with reliquate)

11. Patients refusing to participate in the study

### Setting

Patients will be enrolled at six different surgical units across Italy, tertiary referral centers for both laparoscopy and abdominal wall surgery (three university teaching hospitals). The involved surgeons are experienced in the field of abdominal wall reconstruction and advanced laparoscopic techniques and have treated at least 20 cases for each trial procedure [21].

At least two investigators from each participating center will be involved in the study. One researcher will receive the allocation treatment for the patient after calling the statistician of the main investigation center (University of Genoa). The other investigator, blinded to the randomization arm, will score the primary and secondary postoperative endpoints.

